### Strategies to improve adherence to interventions {11c}

The whole research team including the investigators, research assistants, and research nurses will be required to attend the professional training before recruitment. It is beneficial to ensure the researchers are familiar with the trial administration process and strictly adhere to the study protocol. All the blood samples will be analyzed and check in the research laboratory of Beijing north biotechnology every week. The data collected in this trial will comprise information recorded in the case report forms. Data quality will be checked regularly by research assistants and overseen by monitors. Data monitoring will be conducted regularly with standard operating procedures. All the data modifications are to be marked in the case report forms. If participants withdraw from the trial during the study period, the reasons must be documented and the dropout rate is counted.

### Relevant concomitant care permitted or prohibited during the trial {11d}

All the patients will be operated on by the same general anesthesia. The operation is lumbar surgery. The postoperative medication and nursing will be the same.

### Provisions for post-trial care {30}

No obvious toxic and side effects have been found in the existing studies, but in the course of the study, abnormal damage or unexpected adverse reactions or serious adverse reactions are not excluded, and individual groups are not tolerant or allergic to individual drugs or patches. Adverse reactions related to this study may be observed at any time. In case of any discomfort, new change of condition, or any unexpected situation, whether related to treatment or not, the participant shall inform the investigator in time, and he will make the judgment and medical treatment. Investigators will do their best to prevent and treat. Possible harm due to this study. If there are adverse events related to this study in the clinical trial, the medical expert committee will determine whether it is related to the trial scheme according to law.

### Outcomes {12}

#### Primary outcome

##### The first occurrence and frequency of PONV

The primary outcome will be recorded within the postoperative 48 h. The important index will be self-reported daily and recorded in a diary during the treatment course. In the meantime, each participant will be face-to-face interviewed to attend an in-person assessment at the orthopedic inpatient department.

#### Secondary outcomes

During different time points, the participants will be asked to complete specified physiological tests and self-reported questionnaires.

##### The severity grading of PONV

The severity will be self-assessed using the scores from the visual analog scale (VAS) at pre-operation, postoperative 8 h, 24 h, and 48 h. VAS allows patients to rate the intensity of their symptoms (scored 0, none; scored 1~3, mild; scored 4~6, moderate; scored 7~10, severe).

##### Quality of life

The quality of life will be self-administered using the functional assessment of the SF-12 questionnaire at pre-operation, postoperative 24 h and 48 h. The SF-12 questionnaire measures 12 items, which can be classified as a physical and mental component [25].

##### Blood tests

Blood samples will be collected at pre-operation and postoperative 24 h to measure the levels of serological indicators. The fasting venous blood will be drawn and centrifuged, the separated serum is stored at a – 80 °C refrigerator. Gastric secrete elements and 5-hydroxytryptamine will be analyzed in the research laboratory of Beijing North Biotechnology every week.

### Safety assessment

Adverse events (AEs) are defined as any undesirable experience participants endure during the trial period, regardless of whether or not it is associated with the intervention. The participants will be instructed to report AEs to the research team, and a research nurse will monitor participants for potential occurrences of AEs. All details of AEs, such as time of occurrence, severity, management, and causality to the intervention, will be recorded in the case report forms. All AEs will be followed up from the beginning until resolution.

Current evidence has shown that AHP has a lower rate of adverse drug reactions (ADRs) [19]. However, our trial still pays more attention to possible ADRs, particularly associated with skin lesions (urticaria and pruritus) or other symptoms during the study period.

### Participant timeline {13}

The schedule of events is provided in Fig. 2.

### Sample size {14}

A relatively small number of clinical trials has investigated the effects of acupoint plaster on PONV; however, the research results are not appropriate to calculate the sample size for this study. The sample size is calculated based on the primary endpoint. The small sample-size clinical practice suggests the decreased rate of nausea and vomiting frequency is 60% in the treatment group, while the rate is 40% in the control group based on previous literature. According to the superiority test, it is estimated that at least 69 participants per group are needed when the study achieves 90% power and a two-sided 5% significance level. Given the dropout rate to 20%, the sample size in the clinical trial sets at a total of 166 cases, and each group is 83 cases.

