## Introduction

### Background and rationale {6a}

Postoperative nausea and vomiting (PONV) are some of the most common and undesirable side effects of conventional anesthesia surgery [1–3]. The incidence of PONV after general anesthesia may reach as high as 30~50% [4]. PONV could also lead to serious complications, such as hematoma, surgical incision hemorrhage, pulmonary aspiration, wound dehiscence, and dehydration, aspiration pneumonia, and increased intracranial pressure [5–8]. On the other hand, PONV was likely to reduce patients’ satisfaction, delay discharge and recovery, and increase medical costs [9, 10]. Therefore, unignorable complication still poses a severe challenge for anesthesiologists, clinicians, and researchers.

Existing consensus guidelines from the American Society for enhanced recovery (ASER) recommended a variety of medications that worked at different receptor sites, such as antihistamines, steroids, and so on [11]. However, no single antiemetic drug could fully respond to prophylaxis and management of PONV, and high-risk individuals often did not receive appropriate antiemetic prophylaxis [12]. Besides, traditional drug therapy had its obvious side effects, while the costs of new agents including NK1-antagonists or the newer 5-HT3 antagonists became relatively higher [13, 14]. On the contrary, more and more turned to alternative and complementary medicine, including herbal medications, acupressure, and so on [15–17].

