### Methods in analysis to handle protocol non-adherence and any statistical methods to handle missing data {20c}

Sensitivity analysis was used for the lost causes, and the results of the last observation carried forward or the baseline observation carried forward were used for the sensitivity analysis of the measurement data. The sensitivity analysis of the counting data includes the analysis of the cases in the experimental group and the control group as the ineffective treatment and the best/worst case. In the worst-case analysis, the control group was treated successfully and the experimental group was treated as a failure.

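### The 90% power claim is not established for the primary endpoint: its planning quantity is not a defined outcome, and 60% versus 40% does not give 69 per group

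*Protocol article*

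**What the plan says.** All references are to the protocol article.

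- **Sample size {14}** opens with "The sample size is calculated based on the primary endpoint". The planning assumption is that the "decreased rate of nausea and vomiting frequency is 60% in the treatment group, while the rate is 40% in the control group". The treatment figure is attributed to small-sample clinical practice and the control figure to earlier literature. The result is that "at least 69 participants per group are needed when the study achieves 90% power and a two-sided 5% significance level". Dropout of 20% then brings the size to "a total of 166 cases, and each group is 83 cases".
- **Outcomes {12}** names the primary outcome as "The first occurrence and frequency of PONV", recorded over the 48 hours after surgery. Neither the primary nor the secondary outcomes include a decrease, a percentage reduction or a responder status.
- **Interventions.** Under Experimental group, treatment begins before anesthesia. Both arms receive a plaster and the same antiemetic, so no arm is untreated.
- **Background {6a}** gives the only incidence figure: "The incidence of PONV after general anesthesia may reach as high as 30~50" per cent.
- **Section {20c}** plans a sensitivity analysis of count data that treats "the cases in the experimental group and the control group as the ineffective treatment", plus best-case and worst-case analyses in terms of success and failure. It does not say what counts as either.

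**The concern.** A decrease needs a reference value. PONV cannot occur before surgery, treatment starts before it could occur, and no untreated group supplies a comparison. A reader therefore cannot tell what 60% and 40% are percentages of, or which primary variable they describe. First occurrence (a yes/no or time variable) and frequency (a count) need different planning inputs, and the article gives neither an incidence per arm nor a mean and spread of episode counts.

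The trial describes its hypothesis as confirmatory, and the 90% power figure is the justification for 166 patients. If that figure belongs to no defined endpoint, a null result could be misread as good evidence of no effect. An undefined decrease, success or failure also leaves room to settle the responder rule after the data are seen.

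**Working it through.** **Inputs.** From Sample size {14}: 60% versus 40%, two-sided 5%, 90% power, 69 per group, 20% dropout, 83 per group. From Sequence generation {16a}: 1:1 allocation. From Background {6a}: incidence 30-50%, used only in step 4.

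**1. Is the planning quantity an outcome?** Set side by side, Sample size uses a percentage decrease in frequency, while Outcomes uses first occurrence and frequency over 48 hours. Frequency is common to both; the decrease and its reference are not defined anywhere in the article.

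**2. Try to reproduce 69.** The only reading that can be computed from the stated inputs alone is two plain proportions. With p1 = 0.6, p2 = 0.4 and mean p = 0.5:

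n = [1.960 × √(2p(1−p)) + 1.2816 × √(p1(1−p1) + p2(1−p2))]² / (p1−p2)²

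= [1.960 × 0.7071 + 1.2816 × 0.6928]² / 0.2² = (1.3859 + 0.8879)² / 0.04 = 129.3, so **130 per group**.

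Other versions at 90% power and two-sided 5% give 127 (unpooled), 130 (arcsine) and 140 (continuity-corrected). Relaxed settings do not give 69 either:

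| Setting | n per group |
|---|---|
| One-sided 5%, 90% power | 106 |
| Two-sided 5%, 80% power | 97 |
| One-sided 5%, 80% power | 77 |
| One-sided 10%, 80% power | 56 (66 with continuity correction) |

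Against a control rate of 40%, about 69 per group would correspond to roughly 67% in the treatment group.

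The step from 69 to 83 does reproduce, as 69 × 1.2 = 82.8. However, 20% dropout from 83 leaves 83 × 0.8 = 66.4, slightly under 69; division gives 69/0.8 = 86.25, so 87.

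**3. Power at the stated sizes for 60% versus 40%.**

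Power = Φ{[(p1−p2)√n − 1.960√(2p(1−p))] / √(p1(1−p1) + p2(1−p2))}

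- n = 69: (0.2 × 8.307 − 1.3859)/0.6928 = 0.398, so **65.5%**.
- n = 83: (0.2 × 9.110 − 1.3859)/0.6928 = 0.630, so **73.6%**.

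**4. Illustration on an incidence scale.** The assumptions here are mine: control incidence 30-50% and a 20-point absolute difference, with the same formula.

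| Control vs treatment | 69 per group | 83 per group |
|---|---|---|
| 30% vs 10% | 84.3% | 90.4% |
| 40% vs 20% | 73.2% | 80.9% |
| 50% vs 30% | 67.3% | 75.3% |

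A smaller difference gives much less: 30% versus 20% gives 27% at 69 and 32% at 83.

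Power for first occurrence or for frequency as declared cannot be derived from the article, because it gives no planning value for either.

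**The case against.** The best defence is that Sample size and Outcomes both speak of frequency, so the planning quantity is a loosely worded summary of a primary component, and that a responder definition may sit in the full protocol or analysis plan. The first part stands: a reader might infer that the trial was sized on something unrelated to its primary outcome, and the article does not support that. The second part does not rescue the section. The objection is not to missing detail but to an explicit claim that the inputs are those of the primary endpoint, with a power figure those inputs do not produce.

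Four stronger readings are tempting and should not be drawn.

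- *The quantity cannot be calculated at all.* That is true only of a decrease from a pre-treatment level. A PONV-free proportion, or a change between postoperative periods, could be calculated; the article states neither. The Experimental group text also places sessions at 24 and 48 hours after the operation, which has to be reconciled with a start before anesthesia.
- *60% versus 40% contradicts the 30-50% incidence.* Read as PONV-free proportions, it would imply 60% incidence in controls. But the 30-50% is a general figure for general anesthesia, not a planning value for this operation or for the control arm.
- *Power is really 16-27%.* That comes from treating 60% and 40% as relative reductions from an untreated incidence of 30-50% (18% vs 12% up to 30% vs 20%, at 69 per group). Nothing in the article says so.
- *No plausible scenario reaches 90%.* At 83 per group, 30% versus 10% gives 90.4%. Intention-to-treat analysis with multiple imputation is planned, so 83 is a relevant number, although it is an upper bound if dropouts contribute no information.

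**Conclusion.** The concern holds in this form. The 90% power is not established for the primary endpoint, because the quantity behind it is not a defined outcome and has no stated reference. Taken at face value as two proportions, the inputs support about 65% power at 69 per group and 74% at 83, against about 130 per group for 90%. This arithmetic shortfall is the firmest part, since it needs nothing beyond the section's own numbers and the plain-proportions reading. The 67-84% (69 per group) and 75-90% (83 per group) ranges rest on an assumed control incidence and an assumed 20-point difference, and only illustrate what the trial might deliver. The true power for the declared primary outcome is unknown from this article; it is not shown to be any particular low value.

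**What to change.** Rewrite Sample size {14} as follows:

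1. Name one primary variable from Outcomes {12} as the basis. The proportion of patients with any nausea or vomiting from 0 to 48 hours is one example; a frequency measure would also do if its planning values are given.
2. State the assumed value in each arm and its source, taking into account that every patient also receives an antiemetic, and drop the wording about a decreased rate.
3. Replace the 90% claim with the power that 69 evaluable and 83 randomised per group give over a plausible range of those values.
4. In section {20c}, define ineffective treatment, success and failure in terms of that same variable.

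The cost is wording and a less favourable stated power. No new data collection or added enrolment is required.

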### Objectives {7}

The hypotheses are as follows.

Confirmatory test for AHP versus APP:
H0: Effect of AHP ≤ Effect of APPH1: Effect of AHP > Effect of APP

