### Statistical methods

#### Statistical methods for primary and secondary outcomes {20a}

The efficacy and safety analysis will be conducted according to the intention-to-treat principle. As the third party, the statistical analysis will be performed by the Institute of Clinical Basic Medicine, China Academy of Chinese Medical Sciences, using the statistical packages of social sciences software (SPSS; version 19.0). All the results are based on two-sided tests. Continuous data will be presented as means and standard deviations and compared using the independent *t* test or Wilcoxon’s rank-sum test. On the other hand, categorical data will be presented as percentages and frequencies and analyzed using the chi-square or Fisher’s exact test. The missing values will be implemented by the method of multiple imputations. A *p* value less than or equal to 0.05 will be considered statistically significant.

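### The stated 69 participants per group give about 65% power, not 90%, for 60% versus 40% at two-sided 5%; 90% power needs 127 to 130 per group.

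*Protocol article*

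**What the plan says.** The Sample size section of the protocol article bases the calculation on the primary endpoint. The only effect inputs are two percentages: "decreased rate of nausea and vomiting frequency is 60% in the treatment group, while the rate is 40% in the control group". It names a superiority test and concludes that "it is estimated that at least 69 participants per group are needed when the study achieves 90% power and a two-sided 5% significance level". It then allows for 20% dropout and arrives at 83 per group, 166 in total.

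Other sections fix the rest of the calculation:

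- Sequence generation sets 1:1 allocation.
- The statistical methods section states "All the results are based on two-sided tests" and assigns categorical data to the chi-square or Fisher's exact test.
- The Objectives section presents the comparison as a "Confirmatory test for AHP versus APP".

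No superiority margin, standard deviation or other effect measure is given.

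**The concern.** A 20-point difference centred on 50% is where binomial variance is largest, so 69 per group looks far too few for 90% power. The article prints its inputs and its result side by side, so the claim can be checked from the text alone.

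The 90% figure tells readers that a real effect of the planned size has only a 10% chance of being missed. If the true chance is about one in three, a non-significant result from a trial labelled confirmatory would carry much more weight against the plaster than it deserves. The article describes neither an interim analysis nor a sample-size re-estimation that could correct the shortfall later.

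**Working it through.** **Inputs**

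- p1 = 0.60 and p2 = 0.40, difference 0.20, mean 0.50 (Sample size)
- Two-sided alpha 0.05, z = 1.960; power 0.90, z = 1.2816 (Sample size)
- 1:1 allocation (Sequence generation)
- Superiority margin taken as 0, because none is stated; a positive margin would only raise n

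**Step 1. Can 69 be reproduced?**

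Unpooled variance: n = (1.960 + 1.2816)² × (0.60×0.40 + 0.40×0.60) / 0.20² = 10.51 × 0.48 / 0.04 = 126.1, so 127 per group.

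Pooled variance: n = [1.960×√(2×0.5×0.5) + 1.2816×√0.48]² / 0.20² = (1.386 + 0.888)² / 0.04 = 129.3, so 130 per group.

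The arcsine formula also gives 130, and a continuity correction gives 140. The stated 69 is 69/127 = 54% to 69/130 = 53% of the first two figures.

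**Step 2. Does another convention give 69?**

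| Variant | n per group (unpooled to pooled) |
|---|---|
| Two-sided 5%, 90% power (as stated) | 127 to 130 |
| Two-sided 5%, 85% power | 108 to 111 |
| Two-sided 5%, 80% power | 95 to 97 |
| One-sided 5%, 90% power | 103 to 106 |
| One-sided 5%, 85% power | 87 to 89 |
| One-sided 5%, 80% power | 75 to 77 |

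One-sided 10% gives 81 at 90% power and 56 at 80% (pooled). A one-sample formula at two-sided 5% gives 64 at 90% power and 48 at 80%. None of these is 69.

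**Step 3. What power does 69 give?**

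Pooled normal approximation: power = Φ{[0.20×√n − 1.960×√0.5] / √0.48}.

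For n = 69: (1.661 − 1.386) / 0.693 = 0.398, and Φ(0.398) = 0.655.

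| Evaluable per group | Normal, pooled | Exact, chi-square | Exact, Fisher |
|---|---|---|---|
| 66 (83 less 20% dropout: 83 × 0.8 = 66.4) | 63.5% | – | – |
| 69 (as stated) | 65.5% | 65.7% | 59.1% |
| 83 (all randomised) | about 74% | 74.3% | 69.0% |

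The exact values come from enumerating all outcomes. At 69 per group the type II error is 1 − 0.655 = 0.345 on the chi-square test, against the claimed 0.10.

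**Step 4. What effect does 69 per group detect with 90% power?**

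With the control rate held at 40%, the treatment rate must be about 67.1%, a difference of about 27 points rather than 20.

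**Step 5. What would 90% power need after dropout?**

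Dividing by 0.8: 127/0.8 gives 159 and 130/0.8 gives 163 per group, so 318 to 326 in total against the planned 166.

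**The case against.** The best defence is that 60% and 40% may not be proportions of participants. The phrase "the decreased rate of nausea and vomiting frequency is 60% in the treatment group" is loose, the primary outcome includes a frequency, and the statistical methods section also provides for t tests. If the figures were mean percentage reductions in episodes, n = 2 × 10.51 × SD² / 20². An assumed SD of 36 points gives 68.1, so 69; an SD of 30 gives 48 and an SD of 40 gives 85. So 69 can be reached on that reading.

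This shows a route to 69 but not that it was taken. The SD of about 36 points appears nowhere in the article and was chosen here to fit. The paragraph offers two percentages and nothing else as effect inputs, and the natural reading is two proportions. On the other reading the calculation would lack an essential input. The point that survives is that the paragraph should say what the percentages measure.

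A second objection is that 65% is only one of several possible values. The analysis is by intention to treat with multiple imputation, so power could approach the 74% that applies if all 83 per group were fully observed. That is fair, but the range across tests and attrition is about 59% to 74%, and all of it is well below 90%.

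A third is that the Discussion speaks of preliminary evidence, so a null result might not be over-read. The Objectives section nevertheless calls the test confirmatory, and the stated 90% is wrong however the result is later described.

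**Conclusion.** The concern holds. On the protocol's own inputs, 69 per group gives about 65% power (59% if Fisher's exact test is used), and 90% power needs 127 to 130 evaluable per group. The stated number is a little over half of what is required, and the risk of missing the planned effect is about 35%, more than three times the 10% claimed. Enrolling 83 per group does not rescue it: power is about 74% with no dropout and about 63% with the planned 20%.

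This rests on treating 60% and 40% as independent proportions of participants, compared 1:1 with zero margin by a two-sided 5% test. A positive margin, Fisher's test or a continuity correction would each make the shortfall worse.

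**What to change.** Rewrite the Sample size paragraph as follows:

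1. State that 60% and 40% are proportions of participants meeting a defined criterion, and name the test. If the sponsor meant mean reductions, print the SD and its source and redo the calculation on that basis.
2. Replace the power claim: 69 evaluable per group gives about 65% power for 60% versus 40% at two-sided 5%, and 90% power only for about 67% versus 40%.
3. State that a non-significant primary result will be reported as inconclusive, with the confidence interval for the difference.

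The cost is one paragraph of wording and a less favourable stated power, with no extra patients. The correction is useful at any stage of recruitment. If the 90% claim is to be kept, the evaluable number must be 127 to 130 per group, or 159 to 163 per group randomised with 20% dropout, which is roughly double the planned trial.

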**Methods:**

A multicenter, parallel, randomized controlled trial (RCT) will be conducted. A total of 166 participants will be randomized to either a treatment group receiving an AHP or a control groups receiving an acupoint placebo plaster (APP) in a 1:1 ratio. The primary outcomes are the first occurrence and frequency of nausea and vomiting. The secondary outcomes include the severity grading of nausea and vomiting using a visual analog scale (VAS) measurement system, quality of life, and serological indicators. The safety evaluation is mainly about adverse events and skin reactions’ observation. Assessments will be carried out at the baseline, day 1, and day 2 (the end of the intervention). The central randomization system in the clinical trial (http://124.205.181.142:8082/xwtf/) will be used to conduct random allocation.

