### Assignment of interventions: allocation

#### Sequence generation {16a}

Eligible patients will be randomly assigned to the treatment group or control group in a 1:1 ratio using a central web-based randomization tool. A block randomization sequence using a web-based allocation system will be generated by a central randomization system (http://124.205.181.142:8082/xwtf/).

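### At the stated 20% dropout, 83 per group leaves about 66 evaluable, not the required 69: the figure matches 69 × 1.2 where 69 ÷ 0.8 was needed

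*Protocol article*

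**What the plan says.** The Sample size section {14} of the protocol article builds the enrolment target in two steps. The first gives the number needed for analysis: "it is estimated that at least 69 participants per group are needed", for rates of 60% and 40%, with 90% power and a two-sided 5% level. The second allows for losses: "Given the dropout rate to 20%, the sample size in the clinical trial sets at a total of 166 cases". The same sentence splits this total into two equal arms of 83. The formula for the second step is not given.

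The Methods paragraph of the abstract shows that 166 is the number before any loss: "A total of 166 participants will be randomized". Allocation is 1:1 (Sequence generation {16a}), so 83 per group is the number randomised.

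**The concern.** A dropout rate is a fraction of those who enter the trial. To end with a required number, that number is divided by one minus the rate. Multiplying by one plus the rate gives a smaller answer, and the gap widens as the rate rises. Here the enrolment figure looks like the product of the second method.

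If so, the trial would miss its own minimum under its own dropout assumption, even with full recruitment. Readers use this section to judge whether a null result would be informative, so its figures should agree with each other.

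**Working it through.** **Inputs** (all from Sample size {14}, except where noted)

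- Required per group: 69
- Dropout rate: d = 0.20
- Planned per group: 83, total 166 (the abstract confirms that 166 are randomised)
- Rates: 60% (treatment) and 40% (control); 90% power; two-sided 5%

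**1. Reproducing the plan's figure**

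n × (1 + d) = 69 × 1.2 = 82.8, rounded up to 83; 2 × 83 = 166. This matches exactly.

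n ÷ (1 − d) = 69 ÷ 0.8 = 86.25, rounded up to 87; 2 × 87 = 174. This does not match.

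Multiplication by 1.2 is therefore the likely method, inferred from the match.

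**2. What 83 per group leaves at 20% dropout**

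83 × 0.8 = 66.4. In whole people, 16 losses leave 67 and 17 leave 66. Either is below 69. This step uses only the printed figures and does not depend on the inferred formula.

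**3. What would satisfy both the 69 and the 20%**

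- 86 × 0.8 = 68.8, not enough
- 87 × 0.8 = 69.6, enough

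The gap is 87 − 83 = 4 randomised per group, 8 in total.

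**4. The dropout that 83 per group can absorb**

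(83 − 69) ÷ 83 = 14 ÷ 83 = 16.9%.

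**5. Effect on power, taking the plan's 90% at 69 as given**

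The noncentrality scales with the square root of n:

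(1.960 + 1.282) × √(66/69) − 1.960 = 3.242 × 0.978 − 1.960 = 1.21, and Φ(1.21) ≈ 88.7%.

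The loss is about 1.3 percentage points.

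**6. Effect on power, for the stated 60% against 40%**

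Two-sided 5%, pooled variance under the null hypothesis:

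power = Φ{[0.20 − 1.960 × √(2 × 0.5 × 0.5 / n)] ÷ √[(0.6 × 0.4 + 0.4 × 0.6) / n]}

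| n per group | Standard error under H0 | Standard error under H1 | z | Power |
|---|---|---|---|---|
| 69 | 0.0851 | 0.0834 | 0.397 | 65.5% |
| 66 | 0.0870 | 0.0853 | 0.345 | 63.5% |

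The loss is about 2 points. Both values lie far below 90% because the 69 does not follow from the stated inputs: the same pooled formula gives 130 per group for 90% power. That is a separate error. The dropout step accounts only for the difference between the two rows.

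**The case against.** The strongest objection is one of proportion. The shortfall is about 3 evaluable participants per group. The outcome window is the first 48 hours after surgery in inpatients, recorded by diary and face-to-face interview, and the protocol gives no observed dropout rate, so losses may never come near 16.9%. The powers of 65.5% and 63.5% owe their low level to the defective 69; on the plan's own terms the cost is about 1.3 points. Correcting the dropout step alone would leave a figure that still rests on an unsupported base. All of this stands. It limits the importance of the point but does not make the figures agree.

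A second objection is that the plan analyses by intention to treat with multiple imputation, so 66 is a complete-case count and not the planned analysis set. That is true as a description. However, the plan itself enlarged 69 to allow for dropout, so it treats dropouts as lost information, and imputation does not bring unobserved outcomes back.

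A third is that 20% may have been meant as an addition to 69. The protocol calls it a dropout rate, and its retention section {18b} speaks of counting that rate when participants withdraw. Even on the other reading, the protection obtained is 16.9%, and the sentence would mislead.

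Finally, multiplication by 1.2 is an inference. That also stands, but the shortfall does not need it.

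**Conclusion.** The point holds. A minimum of 69 per group, a 20% dropout rate and 83 randomised per group are mutually inconsistent, whichever formula produced the 83. The shortfall is about 3 evaluable participants per group, or 4 randomised per group. The cost in power is about 1.3 points if 69 is taken to give 90%, and about 2 points at 60% against 40%.

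This assumes that dropout means loss among those randomised and that lost participants contribute no primary outcome. It is a certain error with a modest effect. It is distinct from the larger problem that 69 cannot be reproduced, and it would persist if the base were corrected but the same multiplication kept: 130 × 1.2 = 156 per group, against 130 ÷ 0.8 = 162.5, or 163.

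**What to change.** Restate the last sentence of Sample size {14} in one of two ways:

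- *83 per group (166 in total) retains 69 per group with up to 14 losses per group, a dropout of 16.9%*; or
- *83 per group with 20% dropout leaves about 66 evaluable per group*, followed by the power at that number and the rates and test used. With the stated 60% and 40%, two-sided 5%, pooled formula, that power is 63.5%.

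The second is more informative, because it keeps the stated dropout and shows its consequence. Neither version should repeat the 90% power statement until the base of 69 has been re-derived. Any new base should then be divided by 0.8, not multiplied by 1.2.

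The cost is one sentence, with no change to enrolment. The figure of 87 per group (174 in total) shows the size of the gap. It is not a proposal to recruit more: the Trial status section puts the start of recruitment in May 2018 and expected completion in mid-2020, and 87 per group would not deliver 90% power anyway.
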